## Abstract

**Background:**

The gender gap in time use and its impact on health and well-being are still prevalent. Women work longer hours than men when considering both paid and unpaid (eg, childcare and chores) work, and this gender disparity is particularly visible among parents. Less is known about factors that could potentially mediate or moderate this relationship (eg, work-family conflict and gender role beliefs). Ecological momentary assessment (EMA) allows for the documentation of changes in momentary internal states, such as time use, stress, or mood. It has shown particular validity to measure shorter-term activities (eg, unpaid work) and is thus useful to address gender differences.

**Objective:**

The feasibility of the daily EMA surveys in a parent sample will be examined. The associations between time use, well-being, and stress will be examined, along with potential moderating and mediating factors such as gender, gender role beliefs, and work-family conflict. Finally, the act of monitoring one’s own time use, well-being, and stress will be examined in relation to, for example, the quality of life.

**Methods:**

We conducted a quasi-experimental, nonrandomized controlled trial with 3 data collection methods, namely, online questionnaires, EMA surveys, and qualitative interviews. The intervention group (n=64) will participate in the online questionnaires and EMA surveys, and a subsample of the intervention group (n=6-17) will also be invited to participate in qualitative interviews. Over a period of 1 week, participants in the intervention group will answer daily EMA surveys (4 times per day). In contrast, the control group (n=17) will only participate in the online questionnaires at baseline and after 1 week. The following constructs were surveyed: sociodemographic background (eg, age, gender, and household composition; baseline questionnaire); mediators and moderators (eg, gender role beliefs and work-family conflict; baseline and follow-up questionnaires); well-being, quality of life, and trait mindfulness (baseline and follow-up questionnaires); momentary activity and well-being, as well as state mindfulness (EMA); and feasibility (baseline and follow-up questionnaires as well as interviews). We anticipate that participants will regard the daily EMA as feasible. Particular daily time-use patterns (eg, high paid and unpaid workload) are expected to be related to lower well-being, higher stress, and health-related quality of life. These associations are expected to be moderated and mediated by factors such as gender, gender role beliefs, work-family conflict, and social support. Participants in the intervention group are expected to show higher values of mindfulness, well-being, health-related quality of life, and lower stress.

**Results:**

Patient recruitment started in November 2023 and ended in mid April 2024. Data analysis commenced in mid April 2024.

**Conclusions:**

This study aims to provide valuable insights into the feasibility of using EMAs and the potential benefits of activity tracking in various aspects of daily life.

**Trial Registration:**

Open Science Framework 8qj3d; https://osf.io/8qj3d

**International Registered Report Identifier (IRRID):**

PRR1-10.2196/54728

## Introduction

### Overview

Despite aspirations for gender equality, the “gender gap” continues to be evident in many areas of daily life, including everyday time use and the associated consequences for health and well-being. During the COVID-19 pandemic, this divergence was particularly evident as many women (eg, due to school closures and working from home) felt increased pressures from 2 sides, namely work and family [1]. Overall, time use is an important determinant of health and quality of life. For example, long work hours [2,3], physical and inactive lifestyles [4,5], and informal caregiving for family members [6] are associated with poorer quality of life.

Women, like men, now spend most of their day doing paid work; however, women also do most of the housework, childcare, and unpaid care work [7]. According to Coltrane [8], women’s share of housework is double that of men’s. The largest gender differences are seen among those with children of preschool age [9]. As a result, when paid work and this so-called unpaid work are summed, women (mean 6:44-9:13 hours) work significantly longer hours than men (mean 6:36-8:07 hours) [10]. In terms of leisure time, fathers report more free time than mothers, which is made up of longer uninterrupted periods of rest and is also less often followed by childcare [11]. Gender differences in time use and the impact on health and well-being have been well established in previous research [6,7,10,12,13]. Less is known about how gender and other factors could potentially mediate or moderate the relationship between time use and health and well-being.

### Theoretical Frameworks

There are several theoretical models that explain how people use their time and how this affects their quality of life. One of these theories is the conservation of resources theory [14], which states that people use their time in a way that preserves or enhances their resources (eg, energy, money, or social support). Instead, the time availability theory [15] states that time budgets are dependent on the availability of time and demands in a particular role, while the relative resources theory [16] assumes that time budgets are set depending on the relative power someone has in a relationship or organization. In addition, the work-family conflict model [17] states that time budgets are divided between work and family based on conflicts and demands. The gender perspective—which is often used to complement these theories—is concerned with how gender roles influence time use. For example, the theories of “doing gender” [18] or “gender performativity” [19] highlight how gender roles are constructed through actions and behaviors.

### Survey Methods of Time Use

Generally, diaries are the most common method to measure time use [20,21]. In some cases, self-reports are combined with objective physiological measurements; for example, sleep and wake times are recorded by a motion sensor and well-being is recorded in a diary throughout the day [22]. Ambulatory assessment, such as ecological momentary assessment (EMA), is the measurement of, for example, the mood, symptoms, and activities of individuals in real time and in their natural environment. An advantage of EMA is that it can be used in any situation (eg, on a person’s own smartphone) and allows for the documentation of changes in momentary internal states, such as stress, tension, or mood [23]. Time-use research using EMA has primarily examined individual activities (eg, physical activity [24,25]), yet this methodology has rarely been used to study time-use patterns of different daily activities [26,27].

This is a key research gap because time-use survey techniques differ in that standard survey questionnaires more accurately and reliably measure longer-lasting activities such as paid work, whereas EMA through smartphones is more reliable for shorter-term and less frequent activities (eg, errands and housework) [27]. This means that research questions concerning gender differences in time-use patterns (especially with regard to unpaid activities such as housework and childcare) can be measured more precisely with EMA. Nevertheless, this has rarely been implemented in previous research.

Moreover, introducing EMA to daily activities might focus one’s attention on the present moment, thus increasing state mindfulness. Being present and bringing attention to the present moment is a key component of mindfulness [28,29]. Mindfulness is positively associated with higher levels of life satisfaction, optimism [30], and empathy [31]. It is also negatively associated with, for example, neuroticism [31,32] or difficulties in emotion regulation [33]. Hence, it is likely that regular reflection of and recording of the current activity and associated affect as a momentary and passing state depicts a form of mindfulness exercise [34]. As an exploratory hypothesis, the association between trait, state mindfulness, and daily activities will be examined.

### Research Questions

The planned study will address the relationship between time-use patterns, quality of life, and mindfulness, as well as momentary well-being and stress, with parents as the target group. The theoretical models and factors describing this relationship often neglect the type, duration, and sequence of activities; therefore, they will be complemented using the EMA method.

The EMA method has been used in the target group of parents only to measure specific activities (eg, activities with their own children like supervision and playing together) [35], whereas the measurement of global, daily time use combined with well-being has been used in this context only using student samples [26,27]. Thus, the feasibility of using the EMA methodology with a sample of parents will be examined.

Further, it will be investigated whether the monitoring of daily time use coupled with well-being and stress leads to a change in quality of life and mindfulness. In order to exclude the possibility that these daily mindfulness exercises alone can lead to a change in these constructs, a control group—that does not complete the daily surveys but only the baseline and follow-up questionnaires—will be included.

In summary, the following research questions are examined:

How do parents assess the feasibility of the study design?To what extent do mothers’ and fathers’ time use influence well-being and feelings of stress, and vice versa? Does social support represent a mediator for the above association? Do gender, gender role beliefs, and work-family conflict represent moderators of the abovementioned associations?To what extent does monitoring one’s own time use, well-being, and stress perception influence (1) the quality of life and (2) mindfulness?

## Methods

### Study Design

As this is a pilot study, a quasi-experimental, nonrandomized controlled trial with 3 data collection methods (ie, an online questionnaire [baseline and follow-up], an EMA survey, and interviews) was chosen. The intervention group will participate in the online questionnaires and EMA surveys, while the control group will only participate in the online questionnaires. A subsample of the intervention group will be invited to participate in interviews. The added benefit of recruiting a control group is to investigate whether daily monitoring of time use, well-being, and stress levels has an impact on overall quality of life and mindfulness.

### Participant Characteristics

#### Sample Description

The sample consists of fathers or mothers of at least 1 biological or adopted child who is younger than 18 years of age and living in the household. Participants are included irrespective of sexual orientation and relationship status. A completed informed consent form is also a requirement for inclusion in the study.

The following exclusion criteria will be applied: if participants (1) are younger than 18 years of age, (2) have one or more children with a chronic illness or disability, (3) have one or more foster child or children, and (4) do not own an Android smartphone (intervention group only). Due to technical reasons, only Android users can be included in the intervention group, and since families with a child with a chronic illness differ considerably in their daily routine from families without [36], we decided to exclude them.

#### Sample Size

The minimum sample size for the intervention group was calculated using G*Power (version 3.1.9.6; Erdfelder, Faul, and Buchner; ANOVA, repeated measures, within group, effect size [well-being]=0.25, α=.05, power=0.80, and correlation among repeated measures=0.5), and the target sample size is 64 participants.

For the control group, the target sample size is 17 participants. The sample size was also calculated using G*Power (ANOVA, repeated measures, within-between group, effect size [mindfulness]=0.25, α=.05, power=0.80, and correlation among repeated measures=0.5).

Regarding the number of participants for the interviews, the determination of the number of cases is based on the theoretical concept of data saturation [37]. This means that the sample size should be chosen according to how many interviews are necessary to provide significant new insights into the subject of the study [38,39]. Recommendations on the number of interviews to conduct until data saturation is reached vary from 5 to 60 interviews [37]. Because data saturation in homogeneous samples can be achieved with 6 to 17 cases [37,40], the target subsample size for interviews for this study is 6-17 participants.

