### Analyses

Various between-person factors (eg, age, gender, family composition, and work situation) act as descriptive measures of the sample.

The quantitative material of the questionnaire survey will be analyzed using descriptive analyses to answer the first research question (feasibility of the design). On the other hand, for the evaluation of the open-ended questions in the baseline survey and the interview material, the content analytic approach of Kuckartz [58] is applied. The analysis and coding of the texts or transcripts will be done independently by 2 people. The text sequences or sense units are coded, and categories are derived from these contents or assigned to existing categories. The resulting category systems enable structured processing of the contents.

To answer the second research question (relationship between time use and well-being and stress), variance-analytic and regressive models with repeated measures and multilevel design will be used to analyze within-person change in baseline and follow-up questionnaires as well as to model the sequence of time use, well-being, and stress within the 7-day measurement. In addition, moderator and mediator variables will be considered (eg, gender role beliefs, social support, and work-family conflict).

To answer the third question (influence of monitoring of own time use, well-being, and stress perception on quality of life and mindfulness), within- and between-person models will be used to look at potential differences in the intervention and control groups.

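### The intervention-group target of 64 cannot be reproduced from the G*Power inputs printed for it, which under sphericity require 34 for baseline versus follow-up, so the stated 80% power does not describe the named test at 64

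*Protocol article*

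**What the plan says.** The Sample Size section of the protocol article opens with "The minimum sample size for the intervention group was calculated using G*Power". It names a repeated-measures ANOVA and then gives the inputs and the target in one run: "within group, effect size [well-being]=0.25, α=.05, power=0.80, and correlation among repeated measures=0.5), and the target sample size is 64 participants". It does not give the number of measurements, the number of groups, a nonsphericity correction or a dropout allowance.

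The next paragraph sizes the other arm: "For the control group, the target sample size is 17 participants". That calculation uses a "within-between group, effect size [mindfulness]=0.25, α=.05, power=0.80, and correlation among repeated measures=0.5".

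Three other places bear on the figure:

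- The EMA overview (T1-T7) describes four prompts a day for seven days, an early feasibility look at up to 16 participants, and larger recruitment for piloting, with no number attached.
- The Analyses section plans, under research question 2, repeated-measures and multilevel models to "analyze within-person change in baseline and follow-up questionnaires as well as to model the sequence of time use, well-being, and stress" over the seven days.
- The Research Questions section also asks: "Do gender, gender role beliefs, and work-family conflict represent moderators of the abovementioned associations".

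**The concern.** A reader will take 64 as the output of the listed inputs and 80% as the power of the study's within-person analysis. The inputs look complete enough to rerun, and rerunning them with ordinary settings gives about half of 64. Either an input or allowance is missing from the text, or the figure is wrong. In both cases the printed combination of 64 participants, f=0.25 and 80% power cannot be used to judge what the study can detect.

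The scope of the calculation also matters. The sized test is a mean change over occasions within one group. Research question 2 is mainly about the relation between time use and well-being or stress, with mediation and moderation. Unless the article limits what the 80% refers to, it may be read as covering those analyses too.

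**Working it through.** **Inputs (Sample Size section).** f=0.25, alpha=0.05, power=0.80, correlation rho=0.5, within-factor repeated-measures ANOVA. The number of occasions m is not stated. The design offers 2 (T0 and T8), 4 (prompts per day), 7 (days) or 28 (4 × 7 prompts).

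**Formula (G*Power default effect-size definition).** The noncentrality is λ = f² · N · m · ε / (1 − rho), with df1 = (m − 1)ε and df2 = (N − k)(m − 1)ε. Here k is the number of groups and ε the sphericity parameter (1 under sphericity). Power comes from the noncentral F distribution.

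**Step 1: the control figure, which reproduces.** Take the within-between interaction with k=2, m=2, ε=1.

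- N=34: λ = 0.0625 × 34 × 2 / 0.5 = 8.5, df = 1 and 32, power 0.807.
- N=32 (next smaller even total): λ = 8.0, power 0.781.
- The minimum total is therefore 34, or 17 per group, as printed.

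**Step 2: the intervention figure, same settings.** Take the within factor with k=1, m=2, ε=1.

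- N=34: λ = 8.5, df = 1 and 33, power 0.808.
- N=33: λ = 8.25, power 0.795.
- The minimum is 34, not 64.

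**Step 3: more occasions (ε=1).**

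| Occasions m | Minimum N |
|---|---|
| 2 | 34 |
| 3 | 28 |
| 4 | 24 |
| 7 | 17 |
| 28 | 8 |

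The requirement falls as m rises, so no number of occasions gives 64 under sphericity.

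**Step 4: what 64 delivers for the named test (m=2, ε=1).**

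- At f=0.25: λ = 0.0625 × 64 × 2 / 0.5 = 16, df = 1 and 63, power 0.976.
- Power of 80% is reached at f=0.178: λ = 0.0317 × 64 × 4 ≈ 8.1.
- With 4 occasions, power at f=0.25 is 0.999.

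**Step 5: other routes to 64.**

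- *Lower-bound ε = 1/(m − 1).* Minimum N is 44 (m=3), 50 (m=4), 56 (m=7) and 63 (m=28). For m=28 and N=63, λ = 0.0625 × 63 × 28 / 27 / 0.5 = 8.17 and power is 0.803. Rounding up to two equal groups gives 64. This needs all 28 prompts and the most extreme correction, and neither is stated.
- *Dropout.* Going from 34 to 64 needs a loss of 1 − 34/64 = 47%. No rate is given.
- *Piloting.* Adding up to 16 early participants gives at most 34 + 16 = 50.
- *Correlation 0 instead of 0.5, m=2.* This gives 65 and contradicts the printed input.
- *G*Power's other effect-size options.* These give 128 or 129 (m=2), 79 or 80 (m=3) and 60 or 61 (m=4). They do not use the correlation that the article states.
- *Two independent groups, d=0.5.* This gives 64 per group (power 0.801), but it is not the named test.

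**The case against.** The strongest defence is that the text separates a calculated minimum from a target, and that the EMA overview announces larger recruitment for piloting. A target above a minimum is no contradiction. Epsilon and the number of occasions are also unstated, and the lower-bound correction over the design's own 28 prompts comes to 63, or 64 with even groups. On this view the article is incompletely reported rather than wrong.

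Part of this stands. The documents do not prove that 64 is a mistake, and 34 holds only under sphericity. But minimum and target share one sentence, no other minimum is printed, and no allowance is quantified. The neighbouring figure of 17 fits two occasions with no correction, which makes an extreme correction over 28 prompts a less natural reading. None of these routes makes 64 follow from what is printed.

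A reader might infer three stronger things that the documents do not support:

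- *The study is underpowered for the named test.* With two occasions the reverse is true: 64 exceeds what the inputs need.
- *The sized test serves none of the research questions.* The Analyses section plans within-person change from baseline to follow-up under research question 2, so the test belongs to a planned analysis. The group comparison in research question 3 has its own calculation, for mindfulness.
- *64 was meant per gender, so the comparison of mothers and fathers has half the required number.* This rests on a numerical coincidence. The article claims no power for moderation and gives no gender split. It calls itself a pilot and asks for caution in interpreting associations.

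**Conclusion.** The point holds as a reporting and arithmetic fault of moderate weight, and should be fixed. Assuming sphericity and G*Power's default effect-size definition, the printed inputs give 34 for T0 versus T8 against a stated 64. The stated 80% at f=0.25 is then about 98%, and 80% applies at f of about 0.18. If the authors did use a strong sphericity correction over the 28 prompts, 64 with about 81% power is defensible, but the article would have to say so.

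The calculation supports within-person change in well-being only. It says nothing about the power for the time-use associations, mediation or moderation in research question 2, or for the group comparison in research question 3.

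**What to change.** Rerun the calculation and do one of two things in the Sample Size section.

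1. Restate the figure, for example: the stated inputs require 34 participants for T0 versus T8; the target of 64 gives 98% power at f=0.25 and 80% power at f=0.18.
2. Keep 64 as the result and give the number of occasions, the number of groups, the epsilon and any dropout or piloting allowance that produce it.

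In either case add one sentence saying that the calculation covers the within-person change in well-being. It should say that the calculation does not cover the associations, mediation or moderation in research question 2, or the group comparison in research question 3.

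The cost is one software rerun and one rewritten paragraph. The Results section reports that recruitment ended in mid April 2024; the correction needs no extra participants and no change to the design.

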### Incentives

#### Intervention Group

Participants will be offered an incentive of €35 (US $37.91) for participating in the questionnaires and daily EMA surveys, with an additional €15 (US $16.25) if they complete at least 80% of the daily surveys (ie, €50 [US $54.15] in total). If participants in the intervention group also take part in an interview, they will be offered an additional €10 (US $10.83).

#### Control Group

Participants taking part in the control group, that is, the baseline and final questionnaire, will be offered an incentive of €20 (US $21.66).

### Procedure and Measures

#### Participant Recruitment and Inclusion (T0)

Recruitment will take place through the snowballing method, in which the study will be advertised by means of leaflets through, for example, contacts with parents, parent groups, and relevant organizations (eg, family service centers and counseling centers). An overview of the data collection procedure can be found in Figure 1. An overview of the measures used in the questionnaires and during the EMA surveys can be found in Table 1. See the preregistration for the full questionnaires and interview guides [41].

The study will be advertised through leaflets. These contain a link (eg, by means of a QR code) to a short questionnaire, in which the contact information of the interested parties is collected. This questionnaire is carried out on an online survey platform (eg, SoSci Survey).

Afterward, an appointment is made by phone or email to introduce the study. This takes place digitally (eg, by telephone or video call). First, participants are informed about the study procedure and design. The inclusion and exclusion criteria are checked, and if excluded, they are informed of the reasons for their nonparticipation. If participants do not own an Android smartphone but fulfill all other inclusion criteria, they will be invited to the control group instead. If participants meet the inclusion criteria, they will be asked to download the movisensXS app (movisens GmbH; the survey tool of the EMA part of the study) on their personal smartphone and receive an introduction to its use. During the conversation, they will be given the opportunity to ask questions about the background and the study process. Participants are then sent an email with the link, where they provide written, informed consent. Only then can they access the links to begin the study.

